### Interventions

Patients eligible for the study will be assigned to one of the different groups and will receive one of the following two treatments:

A 5.2 g YQFM injection is diluted into 250 mL of 0.9% sodium chloride injection and administered intravenously once daily for 10 days.The placebo injection, which is a 10 mL 0.9% sodium chloride injection, is diluted into 250 mL 0.9% sodium chloride injection and administered through intravenous drip once daily for 10 days.

All enrolled patients will receive guideline-directed medical therapy in accordance with the Chinese guidelines for the diagnosis and treatment of acute ischemic stroke in 2018 [30]. The treatment measures mainly include lipid-lowering, blood sugar-lowering, and antiplatelet aggregation therapies, and it is required that each hospital maintains the same drug varieties when using medications with similar efficacy.On this basis, the test group received YiQiFuMai lyophilized injection and the control group received 0.9% sodium chloride injection for 10 days. The treatment assignment is illustrated in Fig. 1.

Administration of other TCM or Chinese patent medicines, similar in function and indications with the investigational medicine, and of all traditional Chinese medicine injections will be prohibited during the treatment period. Moreover, during the study period, the use of Chinese herbal decoctions (granules) and other traditional Chinese patent medicines for the treatment of acute ischemic stroke will be prohibited.

If an SAE occurs, a participant or their legally authorized representative requests withdrawal from the study, or a participant does not comply with the prescribed intervention, the investigational drug will be discontinued. Any reasons for discontinuing the intervention will be recorded.

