### Safety outcomes

Safety evaluations include adverse events (AEs), which are any medical events that occur after the subject has received the investigational drug. These events can be manifested as symptoms, signs, diseases, or laboratory abnormalities. It is important to note that AEs may not be causally related to the investigational drug. Additionally, serious adverse events (SAEs) are also evaluated. SAEs include severe outcomes such as death, intracranial hemorrhage, progressive stroke, vascular events.

Laboratory studies (including a complete blood count, routine urine measures, routine stool measures, and measures of liver function, kidney function), vital signs, and an electrocardiogram will be conducted. The causality of adverse events will be determined with reference to the WHO Collaboration Center for International Drug Monitoring, using the criteria of the Uppsala Monitoring Center.

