### Management of adverse events and adverse reactions

We will record any AEs that occur during the course of the study and will assess whether they are related to the investigational drug, properly handled, and tracked until they are resolved, or until the condition stabilizes. AEs and unexpected events will be reported in a timely manner to the Data Security and Monitoring Board, Ethics Committee, and Chief Investigator.

If AEs occur during the trial, the investigator may take necessary treatment measures according to the condition to ensure the safety of the subjects, record them, and decide whether the subjects’ participation should be terminated in the trial. In case of serious adverse events, the subjects should be withdrawn from the clinical trial, and appropriate measures for the subjects should be taken immediately. The insurance for the enrolled subjects will be covered by this study, ensuring the protection of their rights.

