### Data analysis

The missing data are processed by multiple interpolation. If the primary efficacy index is missing, the previous result is carried forward according to the intentionality analysis.If there is a valid value carried forward after randomization, the last observation is used for carry-over.

The main efficacy measure (the percentage of patients with mRS ≤ 2 ) will be compared and analyzed using the chi-squared test. The statistician will perform covariate adjusted analyses and covariate unadjusted analyses. Subgroup analyses will include sex, age, systolic blood pressure, and the baseline NIHSS score.

For dichotomous outcomes, such as the percentage of BI ≥ 90, distribution of mRS scores, proportion of early neurological deterioration, and recurrence rate of stroke, we will use the chi-squared test or Fisher’s exact test to compare the distribution of patients between the two groups.Logistic regression is utilized to estimate the 95% CI. For continuous variables, including neurological function scores, MMSE scores, PRO scale, cerebral blood flow, such as changes from baseline to treatment endpoints, Student’s t-test or Wilcoxon rank-sum test is employed to analyze the differences between the two groups.Survival data will be estimated using the Kaplan-Meier method, survival curves will be plotted, and efficacy will be evaluated using log-rank tests.

According to the safety set data, statisticians compare and analyze the differences in the incidence of adverse events, major adverse events, and liver and kidney dysfunction, as well as routine blood and urine tests between the two groups. For most safety data, Cox proportional-hazards models are used to estimate the hazard ratios between the two treatment groups.

When 50% of the subjects have completed the study, an interim analysis will be conducted. The continuation or suspension of the study is determined according to the analysis results. If the analysis results indicate that valid results cannot be obtained, the study will be terminated immediately. The study will continue if data analysis suggests that efficacy may be achieved at the end of the study.

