Furthermore, this study has two limitations. First, due to funding constraints, we were unable to monitor imaging changes from cranial MRI in each patient. Second, the treatment duration was 10 days, and the follow-up period was 90 days, which is relatively short. These temporal limitations leave the potential impact of YQFM on overall mortality and vascular events uncertain, necessitating further clinical trials with extended follow-up to provide more comprehensive data in this area. In conclusion, the FAST trial aims to deliver high-quality clinical evidence for identifying the target population for YQFM and enhancing clinical efficacy in reducing disability.

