## Appendix C. The visit flow chart

**Table Taba:** 

Procedure Visit Window	Screening	Treatment Phase				Follow-up Phase	
		Day 1	Day 3	Day 7 ± 1	Day 10 ± 1	Day 30 ± 3	Day 90 ± 7
History collection		√					
temperature, heart rate and respiratory rate		√	√	√	√		
OCSP	√						
TOAST	√						
Informed consent	√						
BP	BP was measured and recorded daily					√	√
Inclusion/exclusion criteria	√						
Clinical labs (hematology, chemistry, urine)、biological specimens		√			√		
Serum liver and kidney function test	√				√		
Arterial spin labeling(ASL) test for brain MRI		√			√		
Transcranial Doppler(TCD)		√			√		
Cardiac uhrasonography		√					
ECG		√			√		
carotid artery ultrasonography		√					
mRS	√	√				√	√
NIHSS	√		√	√	√		
BI		√				√	√
MMSE		√					√
Ischemic stroke syndrome factor diagnostic scale		√					
Stroke syndrome factor evaluation scale		√	√	√	√		
PRO					√		
medication administration record			√	√	√	√	√
Adverse events			√	√	√	√	√

Note: Information collection of ASL and TCD completed by 8 research centers with ASL check criteria

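### The Cox safety analysis is named without a risk window or an on-drug/off-drug split, although the drug is given for 10 days and adverse events are recorded to Day 90

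*Protocol article*

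**What the plan says.** All references are to the Protocol article.

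- **Exposure.** Under Interventions, YQFM is "administered intravenously once daily for 10 days". The limitations paragraph of the Discussion confirms that "the treatment duration was 10 days, and the follow-up period was 90 days, which is relatively short".
- **What counts as an event.** Safety outcomes defines "adverse events (AEs), which are any medical events that occur after the subject has received the investigational drug". It gives no end to an on-treatment period.
- **Recording period.** Under Management of adverse events and adverse reactions: "We will record any AEs that occur during the course of the study". The visit chart in Appendix C ticks adverse events at Days 3, 7, 10, 30 and 90.
- **Analysis.** In the safety set, Data analysis first says that "statisticians compare and analyze the differences in the incidence of adverse events, major adverse events, and liver and kidney dysfunction", and adds routine blood and urine tests. It continues: "For most safety data, Cox proportional-hazards models are used to estimate the hazard ratios between the two treatment groups". It does not say which safety variables go into a Cox model, over what period, or whether the ratio may differ between periods.
- **Laboratory schedule.** In Appendix C, the row "Serum liver and kidney function test" is ticked at screening and Day 10. The other clinical laboratory tests and the ECG are ticked at Day 1 and Day 10. None is scheduled later.

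**The concern.** A Cox model with a single treatment term assumes that the ratio of hazards is the same throughout follow-up. Here exposure stops after 10 of 90 days, so 80/90 = 89% of the recording period is off drug. If the injection causes harm mainly while it is being infused, the ratio is above 1 on Days 1-10 and near 1 afterwards. The design itself therefore makes non-proportional hazards likely for such harm. A single ratio fitted to all 90 days would average the two periods, with weight in proportion to where the events fall. After a stroke, complications unrelated to the drug continue well past Day 10 and would add events at a ratio of 1.

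Safety is a stated aim alongside efficacy. A pooled ratio close to 1 could be read as reassurance when the on-treatment data alone would show an excess.

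A smaller point concerns the laboratory data. An abnormality found at the only scheduled post-baseline test, at Day 10, has no meaningful onset time. The phrase about most safety data does not say whether such results are kept out of the Cox models.

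**Working it through.** **No figure to reproduce.** The protocol states no safety event rate, safety hazard ratio or safety power. Every risk below is an assumption, and ranges are shown.

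**Inputs**
- From the protocol: 10 days of drug, 90 days of follow-up, 240 patients per arm.
- Taken as a convention: two-sided 5% level.
- Assumed: on-treatment risk of a first event 5% (placebo) versus 12% (YQFM); the same background risk b in both arms on Days 11-90, with b = 5%, 20% or 50%; no drug effect after Day 10; no dropout.

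**Step 1: on-treatment contrast**
- Hazard ratio = ln(1-0.12)/ln(1-0.05) = 0.1278/0.0513 = 2.49.
- Two-proportion test, 240 per arm, mean risk 0.085. Standard error under no difference = sqrt(0.085 × 0.915 × 2/240) = 0.0255. Standard error under the alternative = sqrt((0.05 × 0.95 + 0.12 × 0.88)/240) = 0.0253. Power = Φ[(0.07 - 1.96 × 0.0255)/0.0253] = about 79%.
- Events by Day 10 = 240 × (0.05 + 0.12) = 40.8. By the events formula used in Step 3, power = Φ[ln(2.49) × sqrt(40.8/4) - 1.96] = about 83%. This is the like-for-like comparator for the Cox figures in Step 3.

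**Step 2: 90-day risks and events**
- 90-day risk = 1 - (1 - on-treatment risk)(1 - b).
- Events = 240 × (sum of the two risks).

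**Step 3: 90-day Cox ratio and power**
- The large-sample value β of the Cox estimate solves ∫[h_T S_T - (h_C S_C + h_T S_T) × S_T e^β/(S_T e^β + S_C)] dt = 0 over Days 0-90. The hazards h are constant within Days 0-10 and within Days 10-90, and S is the event-free proportion (T = YQFM, C = placebo).
- Power = Φ[β × sqrt(events/4) - 1.96].

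| b | Placebo vs YQFM, 90-day risk | Events | 90-day Cox ratio | Power |
|---|---|---|---|---|
| 5% | 9.75% vs 16.4% | 62.8 | 1.77 | 62% |
| 20% | 24.0% vs 29.6% | 128.6 | 1.32 | 34% |
| 50% | 52.5% vs 56.0% | 260.4 | 1.14 | 19% |

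A hand check is to weight the log ratio by the share of events that fall on drug. For b = 20% this gives 40.8/128.6 = 0.317; 0.317 × ln(2.49) = 0.289; exp(0.289) = 1.34, close to the exact 1.32.

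**Step 4: sensitivity to when events occur**

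The same method with a true on-drug ratio of 2.0 and a ratio of 1 afterwards:

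| Placebo risk by Day 10 / Day 90 | Share of placebo events by Day 10 | 90-day Cox ratio | Power, Days 0-10 only | Power, 90 days |
|---|---|---|---|---|
| 10% / 10% | 100% | 2.00 | 82% | 82% |
| 10% / 12.5% | 80% | 1.80 | 82% | 76% |
| 10% / 20% | 50% | 1.51 | 82% | 59% |
| 10% / 40% | 25% | 1.25 | 82% | 37% |
| 2.2% / 20% | 11% | 1.11 | 28% | 8% |

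The loss depends on how many events accrue after Day 10. It is nil when all fall within the dosing period.

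**The case against.** A reader might infer that the plan reduces all safety to one hazard ratio over the whole 90-day record. The text does not say that. It speaks of models and ratios in the plural and fixes no window. Recording events to Day 90 is not the same as deciding to analyse them only over 90 days. Risk windows are commonly set in a statistical analysis plan, and none is shown here. This part of the objection stands, and the point is confined to a method named without a period.

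Nor is Cox the only safety comparison. The preceding sentence plans comparisons of incidence, including liver and kidney dysfunction and routine tests, and causality is assessed event by event. That also stands, so a conclusion that the trial would wrongly call the injection safe goes beyond the text. It does not remove the point, because the incidence comparisons have no window either. A 90-day proportion would be diluted in the same way.

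Dilution is not universal. Reactions that occur only during infusion keep their ratio, as the 100% row shows. The scheduled laboratory tests and ECG end at Day 10, so off-drug time cannot dilute them, and nothing says outright that Cox is applied to them.

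Finally, comparing randomised groups over full follow-up is legitimate for death and vascular events. Making the on-treatment window the main analysis would be a preference. That stands, so the 90-day result should be kept.

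What survives is that the protocol does commit to a proportional-hazards model for most safety data, in a design where the ratio is unlikely to be constant for dosing-related harm.

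**Conclusion.** The point holds in limited form. The protocol chooses Cox hazard ratios for most safety data and sets no risk window or period split, although only 10 of 90 days are on drug. For pooled AE or SAE totals, the natural reading gives a ratio pulled toward 1 when harm is confined to dosing. Under the assumed 5% versus 12% on-treatment risks, about 2.5 becomes 1.77 to 1.14 as background risk on Days 11-90 runs from 5% to 50%. Power falls to 62%-19%, from about 79% for a Day 10 comparison of proportions (83% by the same events formula). The protocol supports none of these rates, so they show direction and plausible size, not an expected loss.

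The documents do not establish that only one 90-day ratio will be reported, that every safety comparison is diluted, or that laboratory results will be put into a Cox model. The matter is a worthwhile improvement to the analysis and not an error that invalidates the safety assessment.

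**What to change.** In Data analysis:

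1. For AEs and SAEs, report the on-treatment period (first infusion to the Day 10 visit) as counts, percentages and a risk difference with 95% CI.
2. Where a Cox model is used for these events, fit separate hazard ratios for Days 1-10 and Days 11-90. Show them beside the 90-day result, which stays for death and vascular events.
3. Limit Cox models to events with an onset date, and compare Day 10 laboratory abnormalities as proportions.

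The cost is analysis wording and a few more tables. AE and medication records are already in the visit schedule, so no new visit is needed; onset dates must be held in the AE record. Each window will contain fewer events, so intervals will be wider. For first events, the Days 11-90 ratio also compares only patients still event-free at Day 10, so it should be read as descriptive.

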## Discussion

Stroke has a significant impact on the physical and mental well-being of patients and is closely linked to high rates of mortality and disability. Additionally, BP tends to rise during the onset of a stroke in order to ensure adequate blood flow to the brain. Previous studies have shown that the optimal range of BP after an ischemic stroke is 155-200mmHg [14], and a BP below this range may lead to more severe brain tissue damage [20, 21]. Improving perfusion is crucial for protecting neurological function and reducing the degree of disability in the treatment of AIS with cerebral tissue hypoperfusion due to inappropriate BP, and there are currently no such therapeutics available.Therefore, it is crucial to discover drugs that can effectively improve perfusion and neurological deficits.

YQFM is manufactured using modern technology. The main ingredients are Panax ginseng, Ophiopogon japonicus, and Schisandra chinensis. This product is widely used in the treatment of acute ischemia cardio-cerebrovascular diseases in China. Studies have reported that YQFM can significantly increase endothelial cell viability and tight junction protein expression, improve blood-brain barrier function [31]. Additionally, YQFM can decrease the mRNA levels of tumor necrosis factor-α, interleukin1β, and interleukin, and can ameliorate the OGD-induced brain microvascular endothelial cell barrier disruption [32]. In addition, YQFM can inhibit excessive autophagy, thereby preventing neuronal damage [33]. YQFM can effectively improve the NFDS score in patients with acute cerebral infarction [27, 28]. However, these data were obtained from a small sample and represent low-quality evidence. At present, YQFM treatment for AIS with inappropriate blood pressure still needs high-quality clinical studies to strengthen the evidence.

Given the current research status, we have designed a large-scale, multicenter, randomized, double-blind, placebo-controlled, parallel-controlled clinical trial to provide higher quality evidence for the safety and efficacy of YQFM in AIS. This study will use the internationally recognized 90-day onset of mRS [34] as the primary outcome measure, with secondary outcome measures including early neurological deterioration, changes in syndrome element scores, daily living activities, MMSE and PRO scale scores. we will evaluate the efficacy and safety of YQFM for the treatment of hypoperfusion-induced cerebral infarction on multiple levels.

Furthermore, this study has two limitations. First, due to funding constraints, we were unable to monitor imaging changes from cranial MRI in each patient. Second, the treatment duration was 10 days, and the follow-up period was 90 days, which is relatively short. These temporal limitations leave the potential impact of YQFM on overall mortality and vascular events uncertain, necessitating further clinical trials with extended follow-up to provide more comprehensive data in this area. In conclusion, the FAST trial aims to deliver high-quality clinical evidence for identifying the target population for YQFM and enhancing clinical efficacy in reducing disability.

## Appendix A. The main ingredients of YQFM

The main ingredients of YQFM were Panax ginseng [Araliaceae; Panax ginseng C.A.Mey.], Ophiopogon japonicus [Asparagaceae; Ophiopogon japonicus (Thunb.)Ker Gawl.], and Schisandra chinensis [Schisandra; chinensis (Turcz.)Baill]. Auxiliary materials were meglumine and mannitol.The specification for each bottle was 0.65 g, which is equivalent to 0.5 g of Panax ginseng, 1.5 g of Ophiopogon japonicus, and 0.75 g of Schisandra chinensis. The bottles were sealed and stored away from direct light. The validity period for the product was 30 months.The drug registration standard number of YQFM is YBZ07062006-2009Z-2015, and the drug approval number, Z20060463, was approved by the State Food and Drug Administration. The batch number of YQFM used in this trial is 20,230,931, which was produced and provided by Tianjin Tasly Pride Pharmaceutical Co., Ltd.YQFM preparations do not contain any restricted drugs or drugs derived from endangered species, and the source of drug materials complies with the code of ethics and national drug administration regulations. More information about YQFM is shown in the Supplementary Material.

## Appendix B. Collection and storage of biological specimens

Biological samples, consisting of one blood specimen and one EDTA-blood specimen, were collected and documented at baseline and 10 days after enrollment. The two blood samples were centrifuged at 3000 rpm at 4 °C for 15 min to separate the plasma and serum, and then stored at -80 °C or in liquid nitrogen. After the study, metabolomics analyses are being performed using the plasma specimens.

## Appendix C. The visit flow chart

**Table Taba:** 

Procedure Visit Window	Screening	Treatment Phase				Follow-up Phase	
		Day 1	Day 3	Day 7 ± 1	Day 10 ± 1	Day 30 ± 3	Day 90 ± 7
History collection		√					
temperature, heart rate and respiratory rate		√	√	√	√		
OCSP	√						
TOAST	√						
Informed consent	√						
BP	BP was measured and recorded daily					√	√
Inclusion/exclusion criteria	√						
Clinical labs (hematology, chemistry, urine)、biological specimens		√			√		
Serum liver and kidney function test	√				√		
Arterial spin labeling(ASL) test for brain MRI		√			√		
Transcranial Doppler(TCD)		√			√		
Cardiac uhrasonography		√					
ECG		√			√		
carotid artery ultrasonography		√					
mRS	√	√				√	√
NIHSS	√		√	√	√		
BI		√				√	√
MMSE		√					√
Ischemic stroke syndrome factor diagnostic scale		√					
Stroke syndrome factor evaluation scale		√	√	√	√		
PRO					√		
medication administration record			√	√	√	√	√
Adverse events			√	√	√	√	√

Note: Information collection of ASL and TCD completed by 8 research centers with ASL check criteria

## Data Availability

No datasets were generated or analysed during the current study.

## Abbreviations

AE: Adverse event
AIS: Acute ischemic stroke
ALT: Alanine aminotransferase
AST: Aspartate aminotransferase
BP: Blood pressure
BI: Barthel index
ECG: Electrocardiogram
eCRF: Electronic case report form
ET: Endothelin
HIF-1α: Hypoxia inducible factor-1α
iNOS: Inducible nitric oxide synthase
MMSE: Mini-mental state examination
mRS: Modified Rankin Scale
NIHSS: National Institute of Health stroke scale
PRO: Patient-reported outcome
ROS: Reactive oxygen species
SAE: SERIOUS adverse event
SCr: Serum creatinine
TCD: Transcranial doppler
YQFM: YiQiFuMai lyophilized injection
